9.1 Adverse Event

An adverse event is any untoward medical occurrence in a clinical study subject administered a pharmaceutical product. An adverse event does not necessarily have a causal relationship with the treatment. An adverse event can therefore be any unfavorable and unintended sign (including an abnormal finding), symptom, or disease temporally associated with the use of a medicinal (investigational) product, whether or not related to the medicinal (investigational) product (ICH GCP).

This includes any occurrence that is new in onset or aggravated in severity or frequency from the baseline condition, or abnormal results of diagnostic procedures, including laboratory test abnormalities.
Note: The sponsor collects adverse events starting with the first study-related procedure (not with the signing of the informed consent). The first study-related procedure might include discontinuation from or decrease in current therapy, a study-specific assessment or scale, or a study-specific procedure (e.g., laboratory test, X-ray, physical examination).

9.2 Serious Adverse Event

A serious adverse event is defined as any untoward medical occurrence that at any dose meets any of the following conditions:

 results in death

 is life-threatening (The subject was at risk of death at the time of the event. It does not

refer to an event that hypothetically might have caused death if it were more severe.)

requires inpatient hospitalization or prolongation of existing hospitalization

 results in persistent or significant disability/incapacity

 is a congenital anomaly/birth defect

Note: Important Medical Events: Medical and scientific judgment should be exercised in deciding whether expedited reporting is also appropriate in situations other than those listed above. For example, important medical events may not be immediately life threatening or result in death or hospitalization but may jeopardize the subject or may require intervention to prevent one of the outcomes listed in the definition above. Any adverse event is considered a serious adverse event if it is associated with clinical signs or symptoms judged by the investigator to have a significant clinical impact.

9.3 Unlisted (Unexpected) Adverse Event

An unlisted adverse event, the nature or severity of which is not consistent with the applicable product information. For an investigational product, the expectedness of an adverse event will be determined by whether or not it is listed in the Investigator's Brochure.

9.4 Associated With the Use of the Drug

Not related
An adverse event which is not related to the use of the drug.

Doubtful
An adverse event for which an alternative explanation is more likely, e.g., concomitant drug(s), concomitant disease(s), or the relationship in time suggests that a causal relationship is unlikely.

Possible
An adverse event which might be due to the use of the drug. An alternative explanation, e.g., concomitant drug(s), concomitant disease(s), is inconclusive. The relationship in time is reasonable; therefore, the causal relationship cannot be excluded.

Probable
An adverse event which might be due to the use of the drug. The relationship in time is suggestive (e.g., confirmed by de-challenge). An alternative explanation is less likely, e.g., concomitant drug(s), concomitant disease(s).

Very likely
An adverse event which is listed as a possible adverse reaction and cannot be reasonably explained by an alternative explanation, e.g. concomitant drug(s), concomitant disease(s). The relationship in time is very suggestive (e.g., it is confirmed by de-challenge and re- challenge).

10.Data Analysis/Statistical Methods

The data will be analyzed by using ANOVA, those do not meet normal distribution will be analyzed by Kruskal-Wallis test. Statistical primary comparisons for SPARCC scores will be made using a repeated measures mixed model with terms for treatment, center and the corresponding baseline values as the covariates. Chi-square will be used for the comparison of proportion rate in different groups.

Analysis is performed for the ITT population and PP population. ITT population is defined as all randomly assigned subjects who received at least 1 dose of test article and had efficacy evaluation after baseline. PP population is defined as the cases that completed all treatment, had no protocol violation and completed all evaluation of study. The efficacy and safety analysis will be performed in the ITT population. And the primary efficacy analysis is also performed for the per-protocol (PP) population

11.Ethics

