2.2 Outcomes

There are two primary outcomes in this study. The first one is to compare the Spondyloarthritis Research Consortium of Canada (SPARCC) score of SIJ and spine from baseline to week 52 in three treatment groups in active AS patients. The co-primary outcome is to compare the Assessment of Spondyloarthritis International Society (ASAS) 20 response rate of three treatment groups at week 52.

Secondary outcomes include ASAS40, ASAS70, ASAS5/6 response rate, ASAS partial remission, Ankylosing Spondylitis Disease Activity Score (ASDAS) remission and ASDAS low disease activity, Bath Ankylosing Spondylitis Disease Activity Index (BASDAI), Bath Ankylosing Spondylitis Functional Index (BASFI), Bath Ankylosing Spondylitis Metroloty Index (BASMI), Masstricht Ankylosing Spondylitis Enthesitis Score (MASES) and safety outcomes.

3.Study design

This is a prospective, open label, active controlled, parallel group study. A total of 150 active AS patients will be randomized in a 1:1:1 ratio into the following three treatment groups: celecoxib 200mg twice a day, etanercept 50mg weekly, celecoxib 200mg twice a day plus etanercept 50mg weekly for 52 weeks. This study will be registered in the Clinical Trials.

4.Subject Selection

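### Continuous outcomes other than the primary SPARCC comparison are assigned ANOVA with no baseline or center term, with a switch to Kruskal-Wallis on an undefined normality check

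*Protocol*

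**What the plan says.** Section 10 (Data Analysis/Statistical Methods) has three sentences on tests.

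- **General rule:** "The data will be analyzed by using ANOVA, those do not meet normal distribution will be analyzed by Kruskal-Wallis test". It names no covariate and no normality test or threshold, and does not say whether week 52 values or changes from baseline are compared.
- **SPARCC:** the primary comparisons use a "repeated measures mixed model with terms for treatment, center and the corresponding baseline values as the covariates".
- **Proportions:** "Chi-square will be used for the comparison of proportion rate in different groups". This covers ASAS20 and the other responder outcomes.

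Section 2.2 makes SPARCC (SIJ and spine) and ASAS20 the co-primary outcomes and lists BASDAI, BASFI, BASMI and MASES among the secondary ones. Section 7.4 adds mSASSS. The schedule in Section 6 has efficacy assessed at screening, at week 0 and at every later visit to week 52, and spinal X-rays at screening, week 24 and week 52. Section 3 sets the size: "A total of 150 active AS patients will be randomized in a 1:1:1 ratio into the following three treatment groups", which is 50 per arm.

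**The concern.** The general rule is the only one left for the continuous outcomes other than SPARCC. Within one section, the protocol treats baseline and center as belonging in the model for one continuous outcome and names neither for the rest, without giving a reason. The baseline measurements exist, so adjustment would need no extra data.

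Two things are at stake. The first is precision: with 50 patients per arm, leaving a correlated baseline out of the model widens every interval for these outcomes. The second is what is being compared. ANOVA addresses means and Kruskal-Wallis addresses ranks. If the choice depends on each outcome's observed distribution, one score may be reported on means and the next on ranks, and nobody can say beforehand which. Once the switch is made, baseline cannot enter as a covariate at all.

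**Working it through.** The protocol gives no figure to reproduce here. It states 150 patients but no alpha, power, effect size or SD, so the correlation, alpha and effect size below are assumptions.

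**1. Precision**

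Inputs: n = 150/3 = 50 per arm (Section 3). The baseline to week 52 correlation r is assumed, over the range 0.3 to 0.7. The SD is taken as equal at both times, with a common slope across arms. In units of SD²:

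- ANOVA on week 52 values: 1
- ANOVA on change: 2(1 − r)
- ANCOVA: 1 − r²

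The ratio of ANCOVA to week 52 ANOVA is therefore 1 − r². The ratio of ANCOVA to change ANOVA is (1 − r²)/(2(1 − r)) = (1 + r)/2.

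| r | Ratio to week 52 ANOVA | Reduction | Ratio to change ANOVA | Reduction |
|---|---|---|---|---|
| 0.3 | 1 − 0.09 = 0.91 | 9% | 1.3/2 = 0.65 | 35% |
| 0.5 | 1 − 0.25 = 0.75 | 25% | 1.5/2 = 0.75 | 25% |
| 0.7 | 1 − 0.49 = 0.51 | 49% | 1.7/2 = 0.85 | 15% |

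At r = 0.5, an unadjusted ANOVA would need 50/0.75 ≈ 67 patients per arm to match ANCOVA with 50.

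In power terms, take two-sided alpha 0.05 (assumed) and the pairwise difference that gives week 52 ANOVA 80.0% power: (1.960 + 0.842) × √(2/50) = 0.56 SD.

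| r | ANOVA, week 52 | ANOVA, change | ANCOVA |
|---|---|---|---|
| 0.3 | 80.0% | 65.8% | 83.6% |
| 0.5 | 80.0% | 80.0% | 89.9% |
| 0.7 | 80.0% | 95.1% | 97.5% |

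ANCOVA is ahead of both versions of ANOVA at each r. Which version it improves on more depends on r, and the protocol does not say which version is meant.

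**2. The switch**

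A simulation used three arms of 50 and a Shapiro-Wilk test on pooled residuals at 5% (assumed, since no test is named). ANOVA was used if the check was passed and Kruskal-Wallis if it failed, with 10,000 runs under no difference. All arms had the same distributional shape.

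| Distribution | Switched to Kruskal-Wallis | Type I error of the two-stage rule |
|---|---|---|
| Normal | about 5% | 5.2% |
| Lognormal | about 100% | 5.2% |
| Gamma | about 100% | 4.8% |
| Exponential | about 100% | 4.6% |

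With one arm shifted by 0.56 SD (4,000 runs, three-group test), power was 81.7% for the two-stage rule against 81.8% for ANOVA on normal data, and 94.0% against 82.2% on gamma data. The switch shows no material inflation and no loss of power in these scenarios. What it changes is the quantity compared.

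**The case against.** Several stronger readings are tempting, and the documents do not support them.

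- **That the primary analysis is affected.** It is not. SPARCC has its own baseline-adjusted model and ASAS20 is binary.
- **That SPARCC is left with two competing primary methods.** The general sentence is followed at once by a specific one for SPARCC, and the specific one governs.
- **That baseline is discarded.** If ANOVA is run on change, baseline is used, though less efficiently than in ANCOVA. The protocol leaves this open. That the ANOVA is unadjusted is the natural reading of the plain term, but the text does not say so in words.
- **That choosing the test from the data inflates type I error.** The simulation gives 4.6% to 5.2%. It covers only arms of equal shape and an assumed normality test, but it offers no support for that charge.
- **That Kruskal-Wallis uniquely denies an estimate.** A three-group F test gives no pairwise difference or interval either, and nothing in the protocol rules out adding them.

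It can also be said that covariates for secondary outcomes are commonly left to a statistical analysis plan, which may exist. That is fair for the choice between week 52 value and change, and for contrasts. It does not dispose of the point, because the protocol itself names the test and the switching rule.

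The strongest remaining argument is that a rank test beat ANOVA clearly on skewed gamma data under a pure shift. The variance reductions above are measured against ANOVA, not against Kruskal-Wallis, so for a strongly skewed score the net gain from ANCOVA is not established. This is a reason to keep a rank-based or bootstrap analysis alongside the adjusted one, but not to let an undefined check pick the main analysis.

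**Conclusion.** The point holds for the continuous outcomes other than the primary SPARCC comparison. As written, Section 10 gives them a less efficient method than the one it chooses for SPARCC, and a switch with no stated criterion.

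The size is a variance reduction of 9% to 49% against ANOVA on week 52 values, or 15% to 35% against ANOVA on change, for r between 0.3 and 0.7. These figures rest on the assumed correlation, equal SDs and a common slope. The documents give no correlation, so no single figure should be quoted as the loss. The effect of the switch is on interpretation (means or ranks, with no baseline covariate possible under Kruskal-Wallis), not on error rates.

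Because neither co-primary outcome is touched, severity is low to moderate. The change is worth making because it is nearly free.

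**What to change.** Restrict the general sentence in Section 10 to the continuous outcomes other than the primary SPARCC comparison, and replace its content as follows:

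- Analyse each of these outcomes by ANCOVA on the week 52 value, or by the same repeated measures mixed model as SPARCC, with treatment, center and the outcome's own baseline. Name one of the two in advance.
- Report pairwise treatment differences with 95% intervals.
- Remove the normality-triggered switch to Kruskal-Wallis.
- Name one sensitivity analysis, either a rank-based ANCOVA or a bootstrap interval, and apply it to all of these outcomes, so that no judgement of skewness is needed to trigger it.

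The cost is a short change of wording and slightly more programming. No additional patients, visits or measurements are needed.

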**Contact details**

[name]

Department of Rheumatology, Third Affiliated Hospital of Sun Yat-sen University

[name]

Telephone numbers: [name]

Trial Protocol

1.Introduction

A number of studies have demonstrated the efficacy of tumor necrosis factor-α inhibitors (TNFi) in reducing inflammation of Sacroiliac Joints (SIJ) and Spine in ankylosing spondylitis (AS) patients. However, the effect of TNFi on retarding radiographic progression in AS patients is still controversial. Interestingly, one clinical trial reported that a strategy of continuous use of NSAIDs (celecoxib) reduced radiographic progression in symptomatic patients with AS. The underlying mechanism is still unknown. It is possible that while the TNFi control inflammation very effectively, it does not have much effect on retarding new bone formation. The NSAIDs on the other hand may not be as effective in controlling inflammation but do inhibit the pathogenic processes involved in bone changes that occur in AS patients. So AS patients may have a better outcome (both control of inflammation and structural changes) if treated with a combination of NSAID and TNFi. This study is designed to assess the clinical and structural outcomes in AS patients treated with a combination of an NSAID (celecoxib) + TNFi (etanercept) versus celecoxib or etanercept alone.

2.Study objective and outcomes

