2.1 Objectives

This study is designed to evaluate the effect of celecoxib and/or etanercept treatment on clinical and structural changes in active AS patients after 52 weeks as measured by clinical, MRI and radiographic assessments. The structural changes seen by MRI and radiographic measures will also be compared and correlated. The safety information will also be collected and analyzed during the study. The safety information includes adverse event (AE), serious adverse event (SAE) and clinically significant abnormal laboratory tests.

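### The primary comparisons are set across three groups and never tied to combination versus each monotherapy, so a significant overall test need not show any benefit of the combination.

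*Protocol*

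**What the plan says.** **The question.** The Introduction (section 1) argues that TNF inhibitors control inflammation well but may do little against new bone formation, that NSAIDs may do the reverse, and that the two together may therefore do better. It ends by saying the study will assess outcomes in patients "treated with a combination of an NSAID (celecoxib) + TNFi (etanercept) versus celecoxib or etanercept alone".

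**The objective.** Section 2.1 is looser. It sets out to "evaluate the effect of celecoxib and/or etanercept treatment on clinical and structural changes in active AS patients after 52 weeks" and names no contrast.

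**The primary outcomes.** Section 2.2 opens with "There are two primary outcomes in this study". The first is the SPARCC "score of SIJ and spine from baseline to week 52 in three treatment groups in active AS patients". The second, called co-primary, is the ASAS20 "response rate of three treatment groups at week 52".

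**The design.** Section 3: "A total of 150 active AS patients will be randomized in a 1:1:1 ratio into the following three treatment groups", which gives 50 per arm.

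**The tests.** Section 10 has three statements:
- a general rule: "The data will be analyzed by using ANOVA, those do not meet normal distribution will be analyzed by Kruskal-Wallis test";
- for the primary SPARCC comparisons, a repeated measures mixed model with treatment, centre and baseline value;
- for rates, and so for ASAS20: "Chi-square will be used for the comparison of proportion rate in different groups".

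No section says which arm is compared with which for the primary conclusion.

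**The concern.** The Introduction's question has two parts: is the combination better than celecoxib alone, and is it better than etanercept alone? The second part is the demanding one, because it isolates what celecoxib adds to a TNF inhibitor. An overall three-group test asks something else, namely whether any arm differs from any other. It can reject because etanercept and the combination are equally good and celecoxib is worse.

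The Introduction itself makes that pattern plausible: it describes TNF inhibitors as very effective against inflammation and NSAIDs as possibly less so. SPARCC scores inflammation on MRI, and ASAS20 includes an inflammation domain. Under a three-group reading, a primary result could be reported as positive in a trial in which celecoxib added nothing to etanercept.

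**Working it through.** **Inputs.** From the protocol: three arms, 150 patients at 1:1:1, so 150/3 = 50 per arm (section 3). Assumed, because the protocol does not state them: two-sided alpha 0.05, ASAS20 response rates, and SPARCC differences in SD units. The sample size of 150 comes with no alpha, power or effect size, so it cannot be reproduced.

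**Scenario.** The combination has exactly the etanercept response rate and celecoxib is lower. The true benefit of adding celecoxib is zero.

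**Overall 3×2 chi-square (2 df, critical value 5.99).** Noncentrality is λ = n·Σ(pᵢ − p̄)² / [p̄(1 − p̄)] with n = 50. Rates are in the order celecoxib/etanercept/combination.

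- 50/60/60%: p̄ = 0.5667, Σ(pᵢ − p̄)² = 0.00667, λ = 0.3333/0.2456 = 1.36, rejection about 17%.
- 50/70/70%: p̄ = 0.6333, Σ = 0.02667, λ = 1.3333/0.2322 = 5.74, rejection 56%.
- 45/75/75%: p̄ = 0.65, Σ = 0.06, λ = 3/0.2275 = 13.19, rejection 91%.
- 50/80/80%: p̄ = 0.70, Σ = 0.06, λ = 3/0.21 = 14.29, rejection 93%.

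Simulated trials agree with these figures to within a percentage point. The overall test reaches 80% rejection only when etanercept exceeds celecoxib by about 24 to 27 points (40% v 67%, 50% v 75.5%, 60% v 83.5%). With three equal rates it rejects in 5%, as it should.

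**Same simulated trials, contrasts instead.** The 2×2 chi-square of combination versus etanercept rejects in about 5% in all four scenarios. Requiring the combination to be significantly better than both monotherapies rejects in 1.6%, 2.3%, 2.5% and 2.6% respectively.

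**Three-group ANOVA.** With combination equal to etanercept and celecoxib d SD away, λ = 50·[(2d/3)² + 2(d/3)²] = 33.3d², on 2 and 147 df. At d = 0.2, λ = 1.33 and rejection is 16%. At 0.3 it is 32%, at 0.5 (λ = 8.33) 73%, and at 0.8 (λ = 21.3) 99%.

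**What the named contrast can detect with 50 per arm.** For ASAS20, power = Φ{[|p₁ − p₂| − 1.96·√(2p̄(1 − p̄)/50)] / √([p₁(1 − p₁) + p₂(1 − p₂)]/50)}. For 60% v 80% this is Φ[(0.20 − 1.96 × 0.0917)/0.0894] = Φ(0.23) = 59%.

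| Etanercept v combination | Power, 50 per arm | Per arm for 80% power |
|---|---|---|
| 60% v 70% | 18% | 356 |
| 70% v 80% | 21% | 294 |
| 60% v 80% | 59% | 82 |
| 70% v 90% | 71% | 62 |

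For SPARCC, the difference detectable with 80% power in a simple two-arm comparison is (1.96 + 0.84)·√(2/50) = 0.56 SD.

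**The case against.** Five points can be made against this.

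- **The primary SPARCC analysis is a mixed model, not a three-group test.** Its treatment term can supply the pairwise contrasts directly, and section 10 speaks of comparisons in the plural. This stands. A reader might infer that the SPARCC method is wrong; the document does not support that. What is missing there is the name of the contrast.
- **The chi-square sentence is ambiguous.** It could mean pairwise 2×2 tests as readily as one 3×2 test. This also stands, so the rejection figures apply to one reading. The other reading does not settle the matter, because the protocol still does not say which pair decides.
- **The size depends on rates that the protocol does not give.** True. A reader might infer that the overall test will be significant even if celecoxib adds nothing. It can be, but at a 10-point gap such as 50/60/60% it rejects in only about 17%.
- **Etanercept versus celecoxib is within scope.** Section 2.1 is broad enough to include it, and the Introduction gives a rationale and not a formal hypothesis. That is a reason to report the comparison, but not to let it stand in for a combination effect.
- **Contrasts and multiplicity rules may be in the SAP, which is not shown.** This matters most for multiplicity. A reader might infer an inflated familywise error from many unadjusted pairwise tests. The protocol does not say that such tests follow or that they would be unadjusted, so that inference is unsupported. The point rests on what the protocol does state: a two-contrast question and primary outcomes framed across three groups.

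**Conclusion.** The concern holds in a limited form. The question in the Introduction and the primary comparisons in sections 2.2 and 10 are not connected: no passage ties the tests to combination versus etanercept and combination versus celecoxib.

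For ASAS20, and wherever ANOVA or Kruskal-Wallis is used as a three-group test, significance can come from the etanercept-celecoxib difference alone. Over the ASAS20 scenarios shown, the chance of this runs from about 17% to 93%, against about 5% for the contrast that isolates celecoxib's contribution. Those figures assume 50 analysed per arm, two-sided 0.05, equal response on etanercept and the combination, and invented response rates.

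For SPARCC the defect is an unnamed contrast in a suitable model. It would go too far to say that the planned analyses cannot answer the question: the mixed model can, and so can pairwise chi-squares. The plan does not commit to them.

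**What to change.** In sections 2.2 and 10:

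1. Name combination versus etanercept and combination versus celecoxib at week 52 as the primary contrasts, estimated from the mixed model for SPARCC and as 2×2 comparisons for ASAS20.
2. State that the combination will be called better than both monotherapies only if both contrasts are significant in its favour. Because both must succeed, no alpha split is needed between these two contrasts.
3. State that a significant three-group test alone does not show a benefit of the combination.
4. Report etanercept versus celecoxib separately from that claim.

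The edit is a few sentences and changes no trial procedure. The real cost is a stricter success criterion with limited power. With 50 per arm, the etanercept contrast on ASAS20 has about 20% power for a 10-point difference and 59 to 71% for a 20-point difference in the cases above. Requiring the celecoxib contrast as well cannot raise that. The protocol should acknowledge this.

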7.2 Safety Assessment

Collect and record AE anytime it occurs. Physical examination, vital sign measurement and laboratory tests such as hematology, urinalogy, blood biochemistry test will be performed.

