7.4 Radiographic assessments

The modified Stroke Ankylosing Spondylitis Score (mSASSS) was used to assess the structural change of AS patients. It assesses the anterior part of the cervical and lumbar spine (from the lower corner of T12 to the upper corner of S1 and from the lower corner of C2 to the upper cornor of T1) as follows: 0= normal; 1= erosion, sclerosis or squaring; 2= syndesmophytes; 3=bridging syndesmophytes (the total score ranges from 0 to 72).

8.Subject Withdrawal

Once a subject is randomized to investigational product, the subject’s vital status will be tracked for the duration of the study. Subjects may choose to discontinue use of investigational product at any time but full accountability at the end of the study is required of all subjects.

If a subject withdraws or discontinued for any reasons prior to last visit, e.g. to withdraw IFC, early withdraw from the study due to AE etc., an early end of treatment assessments listed in ”Early end of treatment” of the study flow chart at the last visit must be completed.

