8.1 Withdrawal from Investigational Product

A subject may voluntarily discontinue investigational product at any time. The investigator may also, at his or her discretion, discontinue a subject from receiving investigational product at any time. Every effort should be made by the investigator to keep the subject in the study. Subjects who are withdrawn from investigational product will be replaced.

The primary reason for subject withdrawal from investigational product will be recorded in the CRF. Primary reasons for withdrawal will be categorized as:

Adverse event
Withdrew consent
Lost to follow-up
Lack of efficacy
Subject reached protocol-defined stopping criteria
Study closed/terminated
Investigator discretion

AS exacerbation may be a reason for withdrawal under lack of efficacy. Specific regard should be given to distinguish withdrawals due to an adverse event and lack of efficacy.

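### Safety is analysed in an ITT set that requires a post-baseline efficacy evaluation, so a dosed subject with no such evaluation is left out of the safety analysis

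*Protocol*

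**What the plan says.** Section 10 of the protocol (Data Analysis/Statistical Methods) names two analysis sets: "Analysis is performed for the ITT population and PP population". The first is defined by three conditions: "ITT population is defined as all randomly assigned subjects who received at least 1 dose of test article and had efficacy evaluation after baseline". The per-protocol set is narrower, since it requires completed treatment, completed evaluations and no protocol violation. The use of the first set is then fixed: "The efficacy and safety analysis will be performed in the ITT population". No safety set is defined anywhere in the protocol.

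Five other places bear on this.

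- Section 3 (Study design) gives size and allocation, "A total of 150 active AS patients will be randomized in a 1:1:1 ratio", and the blinding status, "This is a prospective, open label, active controlled, parallel group study".
- The timetable in Section 6 has efficacy assessed at screening, at weeks 0, 2, 6, 12, 24, 36 and 52, and at early end of treatment. The first scheduled evaluation after baseline is at week 2.
- Section 7.2 says of adverse events: "Collect and record AE anytime it occurs".
- Section 8 requires the early end-of-treatment assessments in this case: "If a subject withdraws or discontinued for any reasons prior to last visit". It also has vital status followed after randomisation.
- Section 8.1 lists adverse event, withdrawn consent and loss to follow-up among the reasons for withdrawal, and adds: "Subjects who are withdrawn from investigational product will be replaced".

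**The concern.** Whether a subject had an efficacy evaluation has no bearing on whether a dose caused harm, yet here it decides whether the subject counts in the safety analysis. The subjects it removes were exposed and then had no further assessment, and an early serious event is one of the reasons that can happen. Safety is part of the stated objectives (Section 2.1) and of the secondary outcomes (Section 2.2). In arms of 50, one uncounted serious event is visible in a table.

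For efficacy, the set is called ITT but inclusion depends on two things that happen after randomisation: taking a dose and being evaluated. Subject and investigator both know the arm, so both events can depend on it. ASAS20 at week 52 is a co-primary outcome, and its denominator is the set in question.

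Replacement of withdrawn subjects makes the loss harder to see. A subject who drops out of the set may be succeeded by one who stays in it, so the number analysed could sit close to plan while dosed subjects are missing.

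**Working it through.** The protocol gives no figure to reproduce on this point, and no dropout or response rate from which to size it. The check is a reading of the set definitions, followed by simple proportions with assumed losses.

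**Who falls outside the safety analysis.** Take a randomised subject who has received at least one dose.

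1. Evaluated at week 2 or later: in the ITT set, and counted.
2. Leaves before week 2 but completes the early end-of-treatment assessments: that visit includes efficacy (Section 6), so the subject is in the set and counted.
3. Leaves before week 2 with no exit evaluation, through death, loss to follow-up or refusal: not in the ITT set, not in the narrower per-protocol set, and so in no stated safety analysis. Any adverse event is still recorded under Section 7.2.

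Only group 3 is affected.

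**Size for safety.** Planned arm size is n = 150/3 = 50. Let k be the number of group 3 subjects in an arm who had a serious event (assumed), and s the number of subjects with a serious event among those retained (assumed). All dosed subjects give (s + k)/n; the protocol's set gives s/(n − k).

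| k | s | All dosed | Protocol's set |
|---|---|---|---|
| 1 | 0 | 1/50 = 2.0% | 0/49 = 0% |
| 1 | 2 | 3/50 = 6.0% | 2/49 = 4.1% |
| 3 | 2 | 5/50 = 10.0% | 2/47 = 4.3% |

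Each omitted event costs 2 points when there is no other event in the arm, and slightly less otherwise (6.0 − 4.1 = 1.9).

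**Size for ASAS20.** Let r be the responders in an arm and k the subjects with no post-baseline evaluation. If those k are kept as non-responders the rate is r/n; if they are dropped it is r/(n − k). With r = 24 (assumed):

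- k = 0 dropped: 24/50 = 48.0%
- k = 1: 24/49 = 49.0%
- k = 3: 24/47 = 51.1%

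For assumed underlying rates of 40% to 80%, the upward shift is 0.8 to 1.6 points at k = 1 (20/49 against 20/50; 40/49 against 40/50) and 2.6 to 5.1 points at k = 3 (20/47 against 20/50; 40/47 against 40/50). These shifts need a non-response rule. Without one, adding the k subjects to the set leaves their week-52 response missing, and an observed-case rate is still 24/47.

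**SPARCC co-primary.** MRI is done at screening, weeks 24 and 52, and early end of treatment. A group 3 subject has no post-baseline score to enter the mixed model with baseline as covariate, so enlarging the set leaves that analysis essentially unchanged.

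**The case against.** The best defence is that very few subjects can be in group 3. Section 8 requires an exit assessment whatever the reason for withdrawal, that visit includes efficacy, and one evaluation is enough for inclusion. This stands, and it limits the size of the problem. It does not remove it, because a required visit cannot be completed by someone who has died, cannot be traced or refuses.

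A second defence is that harms stay visible: adverse events are recorded whenever they occur, vital status is followed, and deaths and serious, unlisted, drug-associated events go to the ethics committee (Section 11.3). This also stands. A reader might infer that early harms go uncollected, and the documents do not support that. The gap is in the set analysed, not in data capture.

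A third is that analysis sets can be left to the statistical analysis plan. That would hold if the protocol were silent, but Section 10 states both the set and its use for safety.

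On efficacy, three stronger readings are tempting and none is supported. A reader might infer that early treatment failures as a group drop out of the analysis; those evaluated at week 2 or at exit remain. A reader might infer a large shift in ASAS20; the loss is assumed and the shift depends on an imputation rule that the protocol does not contain. A reader might suppose that losses fall mainly in the celecoxib-alone arm; the open-label design makes arm-related loss possible, but nothing in the document gives its direction.

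It can also be said that the ITT label is only a name, since the definition is written out. That is fair as to the label, but the conditioning on post-randomisation events remains.

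**Conclusion.** The safety point holds on the plain text. As written, a dosed subject with no post-baseline efficacy evaluation belongs to no set in which safety is analysed. Each such subject with an event lowers that arm's rate by about 2 percentage points, taking the planned 50 per arm. How many there would be cannot be stated from the document, and the exit visit suggests few. The rule should be changed all the same, because the condition is irrelevant to safety and can select against subjects harmed early.

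The efficacy point holds in a lesser form. The set is a modified ITT, and in an open-label trial its two post-randomisation conditions can depend on the arm. The effect is confined to ASAS20 and similar response rates. The 48.0% against 51.1% comparison is an illustration that assumes 24 responders, three subjects lost and a non-response rule. It is not an estimate of bias in this trial, and the arm affected is unknown.

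**What to change.** Change Section 10 in two sentences.

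1. Define a safety set of all subjects who received at least one dose, analysed by treatment received, with no efficacy-evaluation condition, and use it for every safety analysis.
2. For the ASAS20 co-primary outcome, define the ITT set as all randomised subjects in their assigned arm, with missing week-52 ASAS20 counted as non-response. Keep the present set, labelled modified ITT, as a sensitivity analysis.

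It would help to add that subjects who are withdrawn and replaced under Section 8.1 stay in both sets.

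No visit, treatment or data collection changes. The downside is that stated response rates will be slightly lower.
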